#### Secondary outcome measures

Several secondary outcomes are assessed in this study, in line with the recommendations of the 4th International Consultation on Incontinence [57] and the International Continence Society [58]. For each outcome, we have selected measurement instruments that have highest psychometric properties (validity, reliability, and response to change).
*The seven-day bladder diary:* The number of micturition per day/night is monitored to document lower urinary frequency during the day and nocturia [28].
*The 24-h pad test:* This is a validated measure of quantity of urine leakage in 24 h, as measured by the weight of the pads used during a 24-h period minus the weight of the pads before the test. It is identified as a realistic appraisal of the typical urine loss during ordinary daily activity [29]. The upper limit of “normal” for the 24-h pad test has been defined for continent women as being 1.3 g [47].
*The International Consultation on Incontinence Questionnaire (ICIQ) modules:* Five ICIQ modules, known to provide brief and robust measures of UI symptoms, quality of life, and outcome of treatment are used [32].i.
*The ICIQ-Urinary Incontinence short form:* a four-item questionnaire which evaluates the impact of symptoms of incontinence on quality of life and outcome of treatment (0–21 overall score, with greater values indicating increased severity) [30].ii.
*The ICIQ-Nocturia:* a two-item questionnaire which evaluates the impact of symptoms of nocturia on quality of life and outcome of treatment (0–8 overall score, with greater values indicating increased symptom severity) [31].iii.
*The ICIQ-Vaginal Symptoms:* a 14-item questionnaire which evaluates the impact of vaginal symptoms and associated sexual matters on quality of life and outcome of treatment (0–53 vaginal symptoms subscale, 0–58 sexual matters subscale, 0–10 overall impact on quality of life subscale; with greater values indicating increasing problems) [33].iv.
*The ICIQ-Female Lower Urinary Tract Symptoms sex:* a four-item questionnaire for evaluating sexual matters associated with female lower urinary tract symptoms (0–14 overall score, with greater values indicating increasing problems with sexual matters) [34].v.

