*The ICIQ-Lower Urinary Tract Symptoms quality of life:* a 20-item questionnaire which evaluates quality of life in urinary incontinent patients (0–14 overall score with greater values indicating increasing problems). The ICIQ-LUTSqol provides a detailed and robust measure to assess the impact of urinary incontinence on quality of life with particular reference to social effects [32].

*The geriatric self-efficacy index:* A 20-item instrument that enables measurement of whether a person is confident in their ability to prevent urine loss. It has been shown to be a reliable and valid instrument in the aging female population with UI [35].
*The Broom self-efficacy index (Part A):* A 14-item questionnaire to evaluate women's confidence in performing pelvic floor muscle exercise [36]. The Broom self-efficacy index has solid psychometric properties and is a useful tool to measure self-efficacy in doing PFM exercises [59].
*Patient global impression of improvement PGI-I:* a single-item global index used to measure improvement in urinary continence following PFMT on a 7-point scale that ranges from “very much better” to “very much worse.” The PGI-I has shown acceptable convergent and discriminant validity for measuring outcomes in studies of behavioral treatment for UI [37, 60].
*Satisfaction with treatment:* A single-item tool was used to document and capture perceived satisfaction with treatment: “satisfied” (does not need other treatments); “unsatisfied” (would like another treatment for UI) [17].
*PFM strength, morphometry and function:*
i.
*PFM strength on Oxford scale (digital palpation):* The Oxford scale is a 5-point scale used for PFM strength assessment amongst physiotherapists. Laycock and Jerwood have established intra-therapist reliability of this scale, tested in bent-knee lying [38, 61].ii.
*PFM function:* An intravaginal dynamometric speculum, designed by members of our research team is used to measure passive (tone) and active forces (strength), speed of contraction, coordination with cough and endurance [39]. This instrument has been widely assessed for its psychometric properties including its reliability, validity, and responsiveness [39, 62].iii.

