##### Sample size calculation

Sample size was calculated so as to ensure the adequate power and type I error rate for testing the primary hypothesis of non-inferiority of the group-based intervention relative to the individualized intervention, in achieving the relative reduction (in %) in the number of UI episodes at one year. Sample size calculations followed CONSORT Guidelines for non-Inferiority trials [68]. First, based on clinical relevance [69] (minimum clinically relevant difference = 10%) and our pilot data [18–22], we set the “margin of equivalence” (i.e. the upper limit of the non-inferiority interval) as corresponding to a 10% difference between mean % reduction in the number of UI episodes in the “standard treatment” of the individualized intervention minus the group-based intervention arm. This implies that we test the null hypothesis H0:d ≤ 10%, where d denotes the true difference between the mean relative reductions in the number of UI episode in the two arms (individualized minus group-based) against the alternative hypothesis H1:d > 10%. According to the CONSORT guidelines, this choice of the “margin of equivalence” implies that the non-inferiority hypothesis should be rejected whenever the upper bound of the two-tailed (1 – 2α)% confidence interval (CI) for the difference between the two mean % reductions exceeds 10%. In the specific context of a non-inferiority trial, α is the selected risk of a false acceptance of the non-inferiority hypothesis (based on a one-tailed CI-based test, equivalent to an independent-group t-test); i.e. of a false conclusion that a truly inferior intervention is equally efficacious as the “standard treatment” [68].

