#### Data analysis

General analytical strategy: as opposed to conventional superiority trials, in non-inferiority trials per-protocol analysis is generally preferable to intention-to-treat (ITT) analysis, because the postulated hypothesis being tested assumes no difference between the two interventions [68]. Indeed, in non-inferiority trials, a “conservative” approach relies on a per-protocol analysis, which maximizes the probability of finding a statistically significant difference between the two groups, i.e. of rejecting the hypothesis that has motivated the trial. Moreover, the ITT approach includes all individuals who were initially randomized, regardless of their adherence, and thus may dilute, or even mask, the true difference between the interventions in the case of non-adherence or losses to follow-up [59]. In the extreme, if most participants do not adhere to the assigned intervention or fail to complete the follow-up assessment, the ITT analysis will automatically show no difference. To prevent such paradoxes, our main analysis will rely on the per-protocol approach, i.e. include only participants who will have completed the one-year assessment. On the other hand, because of its popularity, we will use the ITT approach in “sensitivity analyses,” as recommended by the CONSORT guidelines for non-inferiority trials [68]. Furthermore, our analyses will focus on (primary or secondary) outcomes at one year. Because all primary and secondary outcomes are measured on continuous scales, the methods outlined below for the analyses of the primary outcome will also apply to all secondary outcomes. However, the analysis of secondary outcomes will be exploratory in nature and some (e.g. for PFM function) may have more limited statistical power.

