Analyses for the primary outcome at one year (and secondary outcomes): The primary analysis will test our main hypothesis that group-based classes are not inferior to individualized treatment with respect to the primary outcome of relative (%) reduction in the number of leakages at one year post randomization. (For all outcomes, the analyses outlined below will be repeated using data on post-intervention assessment.) As recommended for non-inferiority trials, the hypothesis of non-inferiority will be accepted if, and only if, the upper bound of the two-tailed (1-2α) 95% CI (corresponding to a conservative Type I error of 0.025 for the one-tailed independent-group t-test) for the mean difference (in % reduction) excludes the non-inferiority threshold [68], set at 10% difference. This basic analysis will be extended to multivariable analyses. Specifically, two multivariable linear models, of increasing complexity, will be used to adjust the estimated difference between the % reduction at one year in the two groups for, respectively, (1) only the two stratification variables (center and type of UI), as well as the baseline number of UI episodes (to account for regression to the mean phenomenon); and (2) (if necessary) in addition to variables in model (1): any variable, for which a clinically important imbalance between the two arms is revealed by descriptive analyses (see above). In both models, the two-way interactions between the trial arm and (a) center and (b) UI type, will be tested using 1-df model-based F-tests to verify if the difference between the effects of the two interventions depend on either of those stratification variables. In the case of a statistically significant interaction (*p* < 0.05 for the F-test), the intervention effects will be estimated and tested separately in the respective subgroups [79]. The results of multivariable linear regression analyses will be summarized in terms of adjusted mean difference between the outcomes in the two trial arms, together with the 95% model-based CIs. In sensitivity analyses for primary and secondary outcomes at one year, ITT analyses will be conducted, using the same statistical methods.

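### The protocol carries its primary-outcome methods, including the 10% non-inferiority rule, to all secondary outcomes on the premise that all are continuous; for several of them the rule is undefined, has no meaningful margin or could be reversed

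*Protocol article*

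**What the plan says.** Three parts of the protocol article bear on this.

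- **Data analysis, general strategy.** All primary and secondary outcomes are described as continuous. From this the text concludes that "the methods outlined below for the analyses of the primary outcome will also apply to all secondary outcomes". It adds that "the analysis of secondary outcomes will be exploratory in nature".
- **Data analysis, the paragraph headed** "Analyses for the primary outcome at one year (and secondary outcomes")**.** The hypothesis tested is that "group-based classes are not inferior to individualized treatment with respect to the primary outcome of relative (%) reduction in the number of leakages". It is accepted only if the upper limit of the two-sided 95% CI "for the mean difference (in % reduction) excludes the non-inferiority threshold [68], set at 10% difference". Just before this rule, a parenthesis says that the analyses that follow will be repeated, for all outcomes, on the post-intervention data. No other decision rule is given.
- **Sample size calculation.** The 10% margin rests on clinical relevance and pilot data for incontinence episodes. The difference is defined on "the mean relative reductions in the number of UI episode in the two arms (individualized minus group-based").

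The Secondary outcome measures section lists the instruments to which this would apply. The ICIQ modules are scored so that higher is worse; ICIQ-Nocturia, for example, runs 0 to 8, an "overall score, with greater values indicating increased symptom severity". The Broom index measures "confidence in performing pelvic floor muscle exercise". The list also holds a 5-point Oxford scale, a 7-point PGI-I item and a two-category satisfaction item.

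**The concern.** A non-inferiority rule needs a scale on which the effect can be computed, a margin that means something on that scale, and a sign under which a worse new treatment pushes the bound towards the margin. The protocol supplies all three for the primary outcome only. A statistician who follows the text would start each secondary outcome with the same rule, and nothing tells them to change margin, scale or sign.

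The Objectives section lists symptoms, quality of life, self-efficacy, impression of improvement and pelvic floor muscle function as specific objectives, under an overall question of whether group training is not meaningfully less effective. Non-inferiority statements on these outcomes could be cited in favour of group delivery even if they came from a rule that cannot detect a worse group arm.

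**Working it through.** **1. The rule on the primary outcome.** Inputs from Sample size calculation: margin 10, SD 27, true difference 0, one-sided α 0.025, power 90%, 155 per arm. A noncentral-t calculation gives power 0.8997 at 154 per arm and 0.9015 at 155, so the stated 155 is reproduced.

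With d = individualized minus group:

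P(accept) ≈ Φ((10 − d)/SE − t), where SE = SD × √(2/155) and t(0.975; 308 df) = 1.968.

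For SD 27, SE = 3.07 and the CI half-width is 6.03.

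- d = 0: Φ(3.26 − 1.968) = Φ(1.293) = 0.902
- d = 10 (group worse by the margin): Φ(−1.968) = 0.025

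The rule works as intended here. The baseline is also never zero, because Onsite eligibility evaluation requires at least three episodes on the diary.

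**2. The continuity premise.** Secondary outcome measures contradicts it: satisfaction is satisfied or unsatisfied, PGI-I is one 7-point item, and Oxford is a 5-point scale.

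**3. Where % reduction is undefined.** PGI-I rates improvement after training and satisfaction rates the treatment, so neither has a pre-treatment value. Table 1 does not require nocturia, vaginal or sexual symptoms. Baseline scores of 0 are therefore possible on ICIQ-Nocturia (0–8), ICIQ-FLUTSex (0–14) and the vaginal symptoms subscale (0–53), and % reduction then divides by zero.

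**4. Where raw scores are used and 10 is kept as the margin.** ICIQ-Nocturia spans 8 points, PGI-I has 7 levels and Oxford 5, so no true difference can reach 10. ICIQ-UI short form (0–21, higher worse) shows the effect of the sign as well. Let the group be truly 5 points worse, so d = −5, with the SD assumed 3 to 5 (not in the protocol). The expected upper bound is −5 + 0.67 = −4.33 at SD 3 and −5 + 1.12 = −3.88 at SD 5. Both are far below 10, so the rule accepts with probability about 1.

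**5. Where an outcome meant to rise is expressed as % reduction.** A gain is then a negative reduction. If the individualized arm gains 20% and the group arm 10%, d = −20 − (−10) = −10. The SDs are assumptions: 27 is the primary outcome's value and 50 a wider one (SE 5.68).

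| Group arm compared with individualized | d | P(accept), SD 27 | P(accept), SD 50 |
|---|---|---|---|
| gains 20 points less | −20 | about 1.00 | Φ(30/5.68 − 1.968) = 0.999 |
| gains 10 points less | −10 | about 1.00 | Φ(20/5.68 − 1.968) = 0.94 |
| gains 10 points more | +10 | 0.025 | 0.025 |

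The sign reversal does not depend on the SD; only the size of the probabilities does.

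**6. Where the rule points the right way.** For lower-is-better outcomes with a non-zero baseline, such as pad weight as % reduction, a group arm 20 points worse gives d = +20. P(accept) is then below 0.001 for assumed SDs of 27 to 60. For raw higher-is-better scores the sign is also right, and only the margin lacks meaning.

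**The case against.** The strongest reply is that the rule was never meant to travel. Its hypothesis names the primary outcome, it is worded in % reduction, and the margin is tied to incontinence episodes. Shared continuity is a reason to share t-tests, confidence intervals and linear models, not a margin. The protocol never says that self-efficacy or muscle strength will be analysed as % reduction, and it does not state which end of those scales is favourable. The reversal in step 5 therefore rests on an unstated scale and an inferred direction, and its probabilities describe that reading rather than an announced analysis. The specific objectives are to compare the arms, no non-inferiority claim on a secondary outcome is promised, and outcome-specific margins may sit in an analysis plan that is not shown. Results are also to be summarised as adjusted mean differences with 95% CIs, and Pre-treatment covariates provides for adjustment for each outcome's own baseline.

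Much of this stands. A reader might infer that the protocol expressly plans a non-inferiority verdict on every secondary outcome, or that the rule fails on all of them. The documents support neither: the carry-over of the rule comes from general wording, and step 6 shows outcomes where the direction is sound.

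What does not fall away is the text itself. The extension is stated, not omitted. The paragraph heading covers secondary outcomes, the only decision rule sits beneath it without an exception, and the reason given for the extension is contradicted by the protocol's own list of instruments. Calling the analyses exploratory lowers their weight but does not make an undefined or reversed rule usable.

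**Conclusion.** The point holds in limited form. The protocol extends its primary-outcome methods, with their single decision rule, to all secondary outcomes on a premise that is false for at least satisfaction, PGI-I and Oxford.

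Taken literally:

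- the rule is undefined for satisfaction and PGI-I, and wherever a baseline score is 0;
- it has no meaningful margin on raw short scales;
- it is reversed for outcomes meant to increase, if these are expressed as % reduction. A group arm 10 points worse would then pass in about 94% to 100% of trials, and one 10 points better in about 2.5%.

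The last figures assume 155 evaluable per arm, SDs of 27 to 50 and higher-is-better scoring of self-efficacy and strength, none of which the protocol states for these outcomes except the number per arm, which was set for the primary outcome.

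The primary conclusion and the sample size are untouched. The correction is worth making because it prevents unsupported statements on outcomes that the protocol lists among its objectives.

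**What to change.** In both places in the Data analysis section, state that the 10% non-inferiority rule applies to the primary outcome only, and remove the statement that all outcomes are continuous.

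For each secondary outcome, report the between-arm difference on its own scale with a 95% CI, state which direction is favourable, and adjust for the outcome's own baseline where one exists. Use methods suited to type for the two-category satisfaction item and the ordinal PGI-I and Oxford items. Make no non-inferiority statement on a secondary outcome unless a margin specific to it, in its own units, was fixed before unblinding.

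The cost is wording: no new data, no change in sample size and little change in modelling, since adjusted differences with 95% CIs are already planned. The downside is that no formal non-inferiority claim can be made on secondary outcomes, which fits their exploratory status.

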### Onsite eligibility evaluation (1 h)

Women are scheduled for onsite evaluations with a physiotherapist if they report at least three UI episodes on the seven-day bladder diary. After signing the consent form, the Mini-Mental State Examination [48] questionnaire is completed (excludes women with cognitive impairment) and a vaginal exam is conducted to identify any perineal pain or prolapse likely to interfere with either the evaluation or the intervention. Those not eligible for the present study are referred back to their healthcare provider. Eligible participants complete the evaluation and are randomized to either individualized or group PFMT.

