### Outcome measures and moderators/confounders

#### Primary outcome measure

The primary outcome measure is the mean percent reduction in the total number of UI episodes one year post randomization, as measured by a seven-day bladder diary [28]. For example, a participant experiencing four leaks per week pre intervention and two leaks per week at the one-year follow-up would be considered to have had a 50% reduction in leakage episodes. The number of leaks (as measured by the seven-day diary) is considered one of the most reliable measures of success for incontinence treatment and has been widely used in this type of research [16, 28, 44, 47, 51]. Moreover, the reduction in the number of daily leaks, expressed as a percentage, is information that can be easily understood by participants in pre-treatment counseling. As a measurement tool, the seven-day diary has a high compliance rate and good reproducibility [28, 56].

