To err on the conservative side, we relied on the “standard” 95% CI, which corresponds to a stringent one-tailed type I error rate of α = 0.025 (2α = 1–0.95 = 0.05). Similar to other recent non-Inferiority trials (e.g. [70, 71]) and CONSORT guidelines [68], for the purpose of sample size calculation, we assume that the true difference between the mean reductions (%) achieved by the two interventions will be zero (i.e. that they are equally effective). Note that this assumption of equivalence of the two interventions being compared in our trial is consistent with both (a) clinical expectations and (b) (limited) published evidence concerning young and middle-aged UI women [72–74]. Finally, both published trials, which evaluated similar interventions in older women, reported within-group standard deviations (SD) of the individual % reduction scores of about 27% [44, 75]. Accordingly, we assumed SD = 27% in our calculations.

Under the above assumptions, we estimated the sample size needed to ensure high (90%) power to demonstrate the non-inferiority of the group-based intervention (assuming, as mentioned above, that the true difference is 0%). Thus, we calculated N, for which the probability that the upper boundary of the two-tailed 95% CI for the difference in the mean relative reduction (Individual – Group) excludes the “upper threshold of non-inferiority” (10% difference), will reach at least 90%. The sample size calculations were performed using the program in the PASS software package, designed specifically for power/sample size estimation for non-inferiority trials [76]. Under the assumptions outlined above, we will need 155 participants per group, for a total of 310 individuals. We also need to account for possible losses to follow-up, as we expect a 15% attrition rate by the end of the one year, based on both our pilot data and similar published trials [16, 17, 22, 51]. Thus, we will recruit an additional 54 participants per group, increasing the total number of participants to 364 (364*(1–0.15) = 310).

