Preliminary descriptive analyses will compare the individuals in the two trial arms using means, medians, standard deviations, and interquartile ranges (IQR) for continuous variables and frequency distributions for categorical and binary variables. Any variable for which the difference between the two arms is considered clinically relevant will be adjusted for in the multivariable regression analyses (see below). The distribution of the outcome scores will be assessed for normality of residuals, using the Shapiro–Wilk test. In the case of significant violation of normality, appropriate parametric (e.g. logarithmic or Box-Cox) [77] or non-parametric [78] transformation will be applied, to meet the normality assumption underlying the univariate t-tests, as well as multivariable linear regression (see below).

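### The normality-triggered transformation covers the primary t-test, but the 10-point non-inferiority margin is defined only on untransformed percent reduction

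*Protocol article*

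**What the plan says.** **Endpoint.** The Primary outcome measure section reads: "The primary outcome measure is the mean percent reduction in the total number of UI episodes one year post randomization". Its worked example, from four leaks a week to two, is a plain 50% reduction with no transformation.

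**Margin and planning scale.** The Sample size calculation section sets the margin as "a 10% difference between mean % reduction in the number of UI episodes", individual minus group. It assumes an SD of 27% for the individual percent reductions, a true difference of zero, a "stringent one-tailed type I error rate of α = 0.025" and "high (90%) power to demonstrate the non-inferiority of the group-based intervention".

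**Decision rule.** The paragraph of Data analysis on the primary outcome at one year accepts non-inferiority exactly when the upper 95% bound "for the mean difference (in % reduction) excludes the non-inferiority threshold [68], set at 10% difference". It ties that interval to the independent-group t-test.

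**Transformation rule.** The preceding paragraph of Data analysis checks normality of residuals with the Shapiro-Wilk test and continues: "In the case of significant violation of normality, appropriate parametric (e.g. logarithmic or Box-Cox) [77] or non-parametric [78] transformation will be applied". The stated purpose is to satisfy the normality assumption of the univariate t-tests and the linear regressions. The primary outcome is not excepted. The general-strategy paragraph applies the methods for the primary outcome to the secondary outcomes as well.

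**The concern.** The t-test that the transformation is meant to serve is also the test behind the primary decision. If the first instruction is followed after a significant Shapiro-Wilk result, the analysed quantity is no longer percent reduction, and the margin of 10 has no unit there. If the second is followed, the first has been set aside. The article does not say which prevails.

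At stake is the trial's single confirmatory conclusion. The margin must be fixed, in known units, before the data are seen; otherwise the one-sided error rate of 0.025 is not assured. A normality gate also makes the quantity being compared depend on the data: a difference in mean logs or ranks answers a different question from a difference in mean percent reduction.

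**Working it through.** **1. Reproducing the planned size.** Inputs from the Sample size calculation section: margin 10, SD 27, true difference 0, one-sided α 0.025, power 90%.

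n per arm = 2 × (1.960 + 1.282)² × 27² / 10² = 153.2, so 154 by the normal approximation. With the noncentral t distribution, power is 0.8997 at 154 and 0.9015 at 155. The stated 155 per arm (310 in total) is reproduced, and it rests entirely on the untransformed scale.

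**2. Will the trigger fire?** Percent reduction cannot exceed 100 and has no lower limit. Women come to the onsite evaluation "if they report at least three UI episodes on the seven-day bladder diary", and for a woman with three baseline leaks each leak is 100/3 = 33 points. A normal distribution with SD 27 would put these shares above the impossible value of 100:

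| Assumed mean reduction | (100 − mean)/27 | Share above 100 |
|---|---|---|
| 50% | 1.85 | 3.2% |
| 60% | 1.48 | 6.9% |
| 70% | 1.11 | 13.3% |
| 75% | 0.93 | 17.7% |

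Simulated trials agree. All distributions here are assumptions.
- Gamma-shaped remaining leakage, 155 per arm, SD 27, mean reduction 50% to 75%: Shapiro-Wilk on residuals rejected in 100% of runs (2,000 to 4,000 per setting).
- Negative binomial baseline counts of at least 3, mean reduction 70%, SD about 27 to 40: 500 of 500 runs rejected in each of four dispersion settings.

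**3. What does 10 points become on another scale?** Take the log of percent remaining and compare arm means. With individual-arm mean reduction p, the margin is ln[(1 − p + 0.10)/(1 − p)].
- p = 0.50: ln(0.60/0.50) = 0.18
- p = 0.70: ln(0.40/0.30) = 0.29
- p = 0.85: ln(0.25/0.15) = 0.51

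The result also depends on how the log is taken:
- Adding 1 to percent remaining gives ln(61/51) = 0.18, ln(41/31) = 0.28 and ln(26/16) = 0.49 at the same three means.
- Differences in mean logs (again after adding 1), rather than logs of a ratio of means, are 0.22 at 50%, 0.45 at 70% and 0.57 at 75% under the gamma assumption.
- A Box-Cox exponent is estimated from the data (0.13 to 0.31 in these scenarios), so that scale is not known in advance.
- A rank scale has no percentage points at all.

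**4. Is a transformation needed?** In the gamma scenarios, the untransformed t-based interval gave one-sided error of 0.020 to 0.024 at a true 10-point deficit and power of 0.89 to 0.91 at no difference. A separate check with skewed, capped counts, at 500 runs per setting, gave error of about 0.024 to 0.038. The simulation standard error there is √(0.025 × 0.975/500) = 0.007, so 0.038 is within two standard errors of 0.025.

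**The case against.** The strongest reply is that the decision rule already fixes the scale. It makes the interval for the difference in percent reduction both necessary and sufficient for non-inferiority, and endpoint, margin and SD agree with it. The transformation sentence stands in a general paragraph on preliminary descriptive analyses, so the specific rule could be taken to govern. This is a fair reading, and on it the trial has a workable test. But the transformation sentence is mandatory, names the t-tests and makes no exception, so the conflict remains. A separate analysis plan that kept the raw scale would have to depart from this sentence.

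Four stronger readings are tempting, and the documents do not support them:
- *The threshold is lost and the test cannot be carried out.* This takes one of two possible readings as the only one.
- *The number 10 would be applied to log units, so non-inferiority would always be declared, or a margin would be picked after seeing the data.* Nothing in the article says either. They are things an analyst might do if the text is left as it is.
- *Log and Box-Cox are impossible because some values are zero or negative.* They are given as examples beside a non-parametric option, and adding a constant is routine. The difficulty is that the margin does not carry over.
- *Error rates are already inflated.* No error rate for a transformed analysis was computed.

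How clustering by exercise class should enter any bootstrap is a separate matter, not argued here.

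**Conclusion.** The point stands as a conflict between two stated instructions for the primary analysis. The mandatory transformation reaches the primary t-test, whereas the 10-point margin, the SD of 27% and the decision rule exist only for untransformed percent reduction. The conflict follows from the text and needs no simulation.

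That the trigger would very probably fire rests on assumed distributions, although the cap and the discreteness come from the outcome's definition. The spread of log-scale margins, about 0.18 to 0.51, rests on assumed mean reductions of 50% to 85%, because the article states none. The adequacy of the untransformed interval at about 155 per arm also rests on the assumed shapes. The planned sample size is unaffected.

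**What to change.** In Data analysis, remove the normality-triggered transformation for the primary non-inferiority test. State that the primary 95% interval is always for the untransformed difference in mean percent reduction, individual minus group, and that its upper bound is compared with 10 percentage points whatever the Shapiro-Wilk result. An unequal-variance or bootstrap interval on the same scale may be added as an optional check. Report transformed or rank-based analyses as supportive only, with no non-inferiority claim.

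The cost is a few sentences of analysis wording. Margin, sample size and data collection do not change. The change should be dated before any outcome data are examined by arm.
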